### Sample size

Using data available to the end of 2012, the project will be highly powered for the main outcomes, with the ability to detect a minimum relative risk of death (the least common outcome) of 1.12, for each of the three high risk prescribing indices (assuming the following prevalences: DBI 48%; Beers 20% and polypharmacy 30%) [5,15], at 5% significance and 80% power. The incidence of total hospitalisation and hospitalisation for falls and fractures will be greater than the incidence of death, and hospitalisation for adverse drug reactions is similar to the incidence of death. To investigate the relationship between MBS interventions and outcomes, the linkage will be updated annually to increase power. An estimated 5% of people aged ≥ 65 have had a Home Medicines Review; however we are not able to locate estimates for other MBS review items. Assuming 5% exposure over the study period, for the smallest high risk prescribing stratum (Beers: 20%) this would allow detection of a relative change in prevalence of 0.05, comparing *before* and *after* the intervention.

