**Methods:**

The proposed project will utilise data from the 45 and Up Study, a large scale cohort of 267,153 men and women aged 45 and over recruited during 2006–2009 from the state of New South Wales, Australia linked to a range of administrative health datasets. High risk prescribing will be assessed using three indicators: polypharmacy (use of five or more medicines); Beers Criteria (an explicit measure of potentially inappropriate medication use); and Drug Burden Index (a pharmacologic dose-dependent measure of cumulative exposure to anticholinergic and sedative medicines). Individual risk factors from the 45 and Up Study questionnaire, and health system characteristics from health datasets that are associated with the likelihood of high risk prescribing will be identified. The main outcome measures will include hospitalisation (first admission to hospital, total days in hospital, cause-specific hospitalisation); admission to institutionalised care; all-cause mortality, and, where possible, cause-specific mortality. Economic costs to the health care system and implications of high risk prescribing will be also investigated. In addition, changes in high risk prescribing will be evaluated in relation to certain routine medicines-related interventions. The statistical analysis will be conducted using standard pharmaco-epidemiological methods including descriptive analysis, univariate and multivariate regression analysis, controlling for relevant confounding factors, using a number of different approaches.

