### The 45 and Up study cohort

The 45 and Up Study cohort includes 267,153 men and women aged 45 and over from the state of NSW, Australia, randomly sampled from the Medicare Australia database [25]. Participants completed a self-administered postal questionnaire and provided signed consent for participation and follow-up, including linkage to health records (including data on deaths, hospital admissions, and aged care admissions). Recruitment was conducted from February 2006 to April 2009, with an 18% response rate. Following exclusion of individuals with missing data on age and sex, 266,074 participants remained. Of these, 143,199 (54%) are aged 60 years and over (Table 1). Overall, 28% (n = 73,528) of the cohort reported holding a healthcare concession card, hereafter referred as concession card holders. This status will also be confirmed using the health administrative databases. For the purposes of the High Risk Prescribing project, the study sample will be restricted to cohort members who are concession card holders, as this allows full capture of health care utilisation.

**Table 1 T1:** Characteristics of the concession card holders in the 45 and Up study, and total study population

**Characteristic**^ **~** ^	**Concession card holders (n = 73,528; 28%)**	**All participants (n = 266,074)**

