### Ascertainment of outcomes

Data on a range of clinical outcomes will be obtained, including: hospitalisation (first admission to hospital, total days in hospital, cause-specific hospitalisation, covering falls-related hospital admission, and fracture-related hospital admission); all-cause mortality; and, where possible, admission to institutionalised care and cause-specific mortality. Follow-up will be from the date of recruitment, to the last available data on hospitalisation, death or institutionalisation, whichever occurs first. The 45 and Up Study recruitment was from February 2006 to April 2009, giving a range of follow-up duration of 2–5 years, by end 2012 (accounting for linked data delays).

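### The detectable relative risk of 1.12 is presented as the worst case for the main outcomes, but it does not cover cause-specific mortality, which is necessarily rarer than death from any cause

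*Protocol article*

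**What the plan says.** The Sample size section of the protocol article states that "the project will be highly powered for the main outcomes". It supports this with a single number, "with the ability to detect a minimum relative risk of death (the least common outcome) of 1.12", given for all three prescribing indices "at 5% significance and 80% power". The exposure prevalences are 48% (DBI), 30% (polypharmacy) and 20% (Beers). The section then ranks other outcomes against death. Total hospitalisation and admissions for falls and fractures are said to be more common, and "hospitalisation for adverse drug reactions is similar to the incidence of death". Cause-specific mortality does not appear in this ranking.

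The Methods part of the abstract names the main outcome measures. After hospitalisation it lists "admission to institutionalised care; all-cause mortality, and, where possible, cause-specific mortality". The section Ascertainment of outcomes also has cause-specific mortality as an outcome, under the same qualifier: "where possible, admission to institutionalised care and cause-specific mortality".

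The analysis is restricted to concession card holders: "28% (n = 73,528) of the cohort reported holding a healthcare concession card". The article gives no death rate, no list of causes and no share of deaths by cause.

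**The concern.** A single detectable relative risk can stand for a set of outcomes only if it was computed for the rarest of them. The article says that death is the rarest, yet its own outcome list contains one that must be rarer. Every death from a given cause is also a death from any cause, so the count for one cause cannot exceed the total, and it falls below the total as soon as more than one cause occurs. This needs no outside data.

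The stake is interpretation. The cohort is already recruited, so no enrolment decision depends on the sentence. But a null finding for a particular cause of death could later be read against a stated ability to detect 1.12, and so be taken as evidence against a modest association that the study may have had little chance of seeing.

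**Working it through.** **Inputs.** From Sample size: relative risk 1.12, 5% significance, 80% power, exposure prevalence p = 0.48 (DBI), 0.30 (polypharmacy), 0.20 (Beers). From The 45 and Up study cohort: 73,528 card holders by self-report. Assumed, because not stated: a two-sided test, and the share s of deaths due to the cause studied.

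**Step 1: what 1.12 implies.** The figure cannot be strictly reproduced without a death count, so I solve for the count. By the Schoenfeld formula,

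D = (1.960 + 0.842)² / [p(1 − p)(ln RR)²] = 7.849 / [p(1 − p) × 0.01284].

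| Index | p(1 − p) | Deaths needed for RR 1.12 | As % of 73,528 |
|---|---|---|---|
| DBI | 0.2496 | 2,449 | 3.3% |
| Polypharmacy | 0.21 | 2,911 | 4.0% |
| Beers | 0.16 | 3,820 | 5.2% |

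The two-proportion formula gives a similar order for Beers, about 3,470 deaths. A one-sided test would need 3,009 (4.1%).

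**Step 2: is 1.12 coherent across the three indices?** With one set of 3,820 deaths, the detectable relative risk, exp(2.802 / √[D p(1 − p)]), is 1.095 for DBI, 1.104 for polypharmacy and 1.12 for Beers. So 1.12 works as one worst-case value for all-cause death.

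**Step 3: cause-specific death.** Replacing D by sD gives

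ln(detectable RR) = 2.802 / √[sD p(1 − p)].

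Where D is just enough for 1.12, this reduces to ln(1.12) / √s. In that case the inflation does not depend on the prevalence, the sidedness or the death count. For Beers with D = 3,820:

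| Assumed share of deaths | Events | Detectable RR at 80% power | Power at RR 1.12 |
|---|---|---|---|
| 100% | 3,820 | 1.12 | 80% |
| 50% | 1,910 | 1.17 | 51% |
| 30% | 1,146 | 1.23 | 34% |
| 10% | 382 | 1.43 | 14% |

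Worked line for 30%: 0.16 × 1,146 = 183.4; √183.4 = 13.54; 2.802 / 13.54 = 0.207; exp(0.207) = 1.23.

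With the same 3,820 deaths, shares of 50%, 30% and 10% give 1.15, 1.20 and 1.37 for polypharmacy, and 1.14, 1.18 and 1.33 for DBI. All exceed 1.12.

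**The case against.** The strongest reply is that cause-specific mortality is conditional. Both places that list it say it will be studied only where possible, and the power section attaches 1.12 to death, not to death from a cause. Among the outcomes which that section actually compares, calling death the rarest is plausible. This lowers the weight of the point but does not remove it: the qualifier makes the outcome conditional, not more frequent, and the power claim is worded for the main outcomes without that limit.

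A second reply is that sensitivity may still be good. This stands in part. Under the assumptions above, a cause with 30% of deaths has 86% power at a relative risk of 1.25. A reader might infer that the claim of high power is simply untrue, but the article sets no target effect and gives no cause-specific rates, so it cannot be shown false.

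Other stronger readings also fail:

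- **Institutionalisation.** A reader might infer that it is underpowered too. Its incidence is not given, and nothing in the article shows that it is rarer than death.
- **One figure for three prevalences.** A reader might think 1.12 cannot serve 48%, 30% and 20%. Step 2 shows that it can, as the value for the smallest exposure group.
- **Adverse-drug-reaction admissions.** A reader might say the power section ranks an outcome that is not listed. Ascertainment of outcomes names only falls and fractures under cause-specific hospitalisation, but that category can include such admissions.

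**Conclusion.** The point holds as a limit on the scope of the power statement. All-cause death is not the least frequent of the listed main outcomes, so 1.12 is not a worst case for all of them, and the claim of high power is unsupported for cause-specific mortality.

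That all-cause death is not the rarest follows from the article's own outcome list and rests on no assumption. The size does rest on assumptions: that 1.12 is the Beers value at two-sided 5%, that deaths number about 3,820, and that a cause makes up 50% to 10% of them. The detectable relative risk is then about 1.17 to 1.43. These shares are illustrative; the study's own causes could lie inside or outside this range.

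The figure of 1.12 for all-cause death is not in dispute, nor is its use for the hospitalisation outcomes that the article describes as more common than death or similar to it.

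**What to change.** In the Sample size section:

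1. Delete the parenthesis that calls death the rarest outcome, or restrict it to the outcomes compared in that section.
2. State that 1.12 refers to all-cause mortality and also bounds the hospitalisation outcomes said to be at least as common. Falls and fracture admissions stay within the claim.
3. Give the number of deaths assumed. If 1.12 is the Beers value at two-sided 5%, this is about 3,820, or 5.2% of 73,528. If another basis was used, state that count and the sidedness.
4. Either give a separate detectable relative risk for cause-specific mortality, using the cause shares the study expects, or exclude it explicitly from the power claim. The shares used above are for illustration and should not be printed as the study's own.

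The cost is a few sentences and, if the first option in item 4 is taken, one short calculation. Design, data and analysis do not change. The stated sensitivity becomes less favourable for cause-specific death.

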### Ethical considerations

This study has been approved by the NSW Population and Health Services Research Ethics Committee (approval no. 00410). In addition, the 45 and Up Study also has overarching in principle ethical approval for data linkage from the University of New South Wales Human Research Ethics Committee (approval no. 05035), Sydney, Australia and the Department of Health and Ageing, Ethics Committee (approval no. 1/2005).

### Study cohort characteristics

The baseline characteristics of the 45 and Up study participants, and concession card holders are presented in Table 1. In this sample, 54% were female, 75% of participants were born in Australia and 75% were married or in a de facto relationship. In relation to lifestyle and social factors, 32% reported less than weekly alcohol use and 7% were current smokers. Of the total population, 37% were classified as overweight and 21% as obese. Excellent self-reported health was reported by the 15% of the population, and 68% had low psychological distress. In the 45 and Up Study cohort, concession card holders were generally older, had fewer educational qualifications, were more likely to be overseas born and not married, compared to other cohort members. In terms of functional capacity, concession card holders were more likely than non-card holders to report having a major disability, fair or poor self-reported health status, very high psychological distress and comorbidities.

## Discussion

High risk prescribing is a term used to describe a pattern of prescribing, which, for theoretical or empirical reasons, has been linked with adverse outcomes in older people. Identifying strategies to minimise high risk prescribing in older people requires a reliable evidence base on the magnitude of the problem and the relationship of high risk prescribing to adverse health outcomes, as well as the effectiveness of routine interventions to improve quality use of medicines. The Australian health system is well suited to this, because of a rich collection of large population-based and administrative databases. The size of the 45 and Up Study, along with linkage to routine health data will allow investigation of the relationship between high risk prescribing and adverse outcomes at the population level, including exploration of confounding, effect modification and intervention effects. In addition, opportunities to utilise other population-based datasets, including general PBS population and Department of Veteran Affairs’ data will also be explored.

It should be noted that the administrative datasets are not collected specifically to describe patterns of medicine utilisation or medical care and there are some important limitations to this cohort analysis, including generalisability, validity of data, bias and causality issues. Cohort studies often involve selected groups and produce results based on internal comparisons within the cohort. Theoretical and empirical work have shown these internal comparisons to be valid and reliable [37,38], including research from the 45 and Up Study [39]. The durability of findings from cohorts such as the British Doctors’ Study [40] is further testament to the robustness of this approach. The 45 and Up Study is not designed to be representative of the general population and the response rate to the baseline questionnaire was 18%, meaning that although relative risks calculated from internal comparisons, such as outcomes in relation to different categories of high risk prescribing, are valid and robust, caution should be exercised when generalising from the individual prevalences of exposure and other cohort attributes. Furthermore, variables from the 45 and Up Study questionnaire are self-reported and vary in their validity. However, the utilisation of established questionnaire instruments and population-level measures may minimise the possibility of bias [25].

While the gold standard for evaluating the causal effects of medicines on clinical outcomes is the randomised controlled trial, randomising older individuals to high risk prescribing would be inappropriate. Therefore, observational studies are essential to elucidate the association between high risk prescribing and health outcomes in this population, and to ensure the necessary degree of heterogeneity. However, the quantification of causality requires judicious interpretation of observational data [2]. A central issue is confounding, particularly by indication, in that individuals with high risk prescribing are likely to differ from others in ways that will affect disease risk. Awareness of this issue, along with using multiple analytic approaches to quantify potential biases is essential, particularly to examine the robustness of the findings with different assumptions and methods. Finally, it is important to avoid the assumption that any observed relationship of high risk prescribing to adverse outcomes is necessarily causal; a key focus of the project is to quantify variation in outcomes according to different patterns of medicines use, from the point of view of disease burden and consequences for the health system, rather than from a direct aetiological perspective.

In summary, the 45 and Up Study and its linkage with health databases will allow investigation of the relationship between high risk prescribing and adverse outcomes at the population level, which has not been possible in the past. The proposed study will generate an important, unique dataset for the quality use of medicines and will allow the identification of targets for improving prescribing in older people.

## Abbreviations

ACCMIS: Aged and Community Care Management Information System; APDC: Admitted Patients Data Collection; ATC: Anatomical Therapeutic Codes; CHeReL: Centre for Health Record Linkage; DBI: Drug Burden Index; MBS: Medicare Benefit Scheme; NSW: New South Wales; PBS: Pharmaceutical Benefit Scheme; TGA: Therapeutic Goods Administration.
